### 2.8. Data Curation and Statistical Analysis

Stata 16 (StataCorp LLC, College Station, TX, USA) will be used for data curation and statistical analysis. Data will be curated by one author [name] ([name]), who will assign neutral names randomly to the e-learning group and the video group. The curated DTA file will then be transferred to another author [name] ([name]) for data analysis.

A univariate linear regression will be used to analyze the primary outcome. Then, a multivariable linear regression model will be generated with profession, prior NIHSS knowledge, and work center as adjustment variables. The conditions of application will be checked, i.e., the residues distributions normality assessed graphically on a histogram and the homoscedasticity using the residual-versus-fitted plot function in Stata.

The analysis of the same quiz undertaken one month later (knowledge retention) will follow the same procedure as the primary outcome.

The assessment of the distribution of the other continuous variables, i.e., time for course completion and time for quiz completion, will be done graphically and using the Shapiro–Wilk test in case of doubt. Data will be described as means (95%CI) or median (Q1–Q3) depending on what is applied. Then, a Student’s unpaired t-test or the Mann–Whitney U test will be applied.

The cross-sectional assessment of the performance in the pre-course 50-question quiz will be described overall and according to profession and prior NIHSS experience.

A sensitivity analysis will be performed by excluding those who have previously followed either the e-learning module or the video from Patrick Lyden [20].

User satisfaction, user course duration perception, and probability of recommendation will be assessed using a 5-point Likert scale and analyzed graphically, then using the Fisher’s exact test.

The data file will be uploaded to the Mendeley Data repository.

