## Abstract

The National Institutes of Health Stroke Scale (NIHSS) is commonly used to triage and monitor the evolution of stroke victims. Data regarding NIHSS knowledge in nurses and physicians working with stroke patients are scarce, and a progressive decline in specific knowledge regarding this challenging scale is to be expected even among NIHSS certified personnel. This protocol was designed according to the CONSORT-eHealth (Consolidated Standards of Reporting Trials) guidelines. It describes the design of a randomized controlled trial whose primary objective is to determine if nurses and physicians who work in stroke units improve their NIHSS knowledge more significantly after following a highly interactive e-learning module than after following the traditional didactic video. Univariate and multivariable linear regression will be used to analyze the primary outcome, which will be the difference between the score on a 50-question quiz answered before and immediately after following the allocated learning material. Secondary outcomes will include knowledge retention at one month, assessed using the same 50-question quiz, user satisfaction, user course duration perception, and probability of recommending the allocated learning method. The study is scheduled to begin during the first semester of 2022.

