### 2.2. Online Platform

An internet-based and GDPR (General Data Protection Regulation)-compliant study platform will be created using the Joomla 3.9 content management system (Open Source Matters, Inc., New York, NY, USA) [27]. Randomization will be stratified according to professional status (nurse or resident physician), prior NIHSS knowledge (limited, moderate, or extended), and institution by virtue of specific links displayed on the front page. Clicking on the appropriate link will automatically randomize the participant into one of two groups (video or e-learning) through the use of Gegabyte’s Random Article module [28]. A specific and straightforward registration form (Membership Pro, Joomdonation [29]) will then be displayed. Participants will have to enter and confirm a valid e-mail address, choose a secure password, and validate a captcha field. After clicking on the “Register” button, a generic email containing a data policy statement will be sent to the email address entered by the participant. Simultaneously, the participant will be automatically logged in and a first questionnaire will be displayed.

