### 2.3. First Questionnaire

This questionnaire (Table 1) is designed to gather all relevant demographic information regarding the participant and to obtain data regarding their prior NIHSS training and knowledge. It will be administered using the Community Surveys 5.6 component (CoreJoomla) [30].

Regular expression (Regex) rules will be used to avoid invalid data entry. A 5-point Likert scale (very low/not at all to very high/very much) will be used to record appropriate data.

After completing this first questionnaire, participants will be redirected to a first 50-question quiz designed to assess their baseline knowledge. This quiz is identical to the one used in our previous studies [18,19]. After completing this quiz, participants will be shown the training material they have been allocated to.

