### 2.6. Outcomes

The primary outcome will be the difference between the score on the 50-question quiz answered before and after following the allocated learning material. Secondary outcomes will be the overall performance in the pre-course 50-question quiz according to profession and prior NIHSS experience, performance in the same quiz undertaken one month after completion of the learning material (knowledge retention), time to course and quiz completion, user satisfaction with the learning method, user perception of the duration of the course, and probability that the user would recommend the learning material they have been allocated to a colleague.

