### 2.7. Participants and Sample Size

Seventy-two participants are required to have 80% chance of detecting a difference of 2 points in the post-course 50-question quiz between groups at the 5% significance level. A total of 120 invitations should be sent, and a participation rate of 60% will therefore be required.

Disclaimers and data policy statements will be displayed on the front page and on the registration page (through a link that will open these statements in a modal).

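### The primary outcome is a raw change score and neither planned regression adjusts for the baseline quiz score: valid, but less precise than a nearly free alternative

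*Protocol article*

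**What the plan says.** Section 2.6 defines the endpoint: "The primary outcome will be the difference between the score on the 50-question quiz answered before and after following the allocated learning material". Section 2.8 then gives two models in sequence. The first is stated as "A univariate linear regression will be used to analyze the primary outcome". In the second, "a multivariable linear regression model will be generated with profession, prior NIHSS knowledge, and work center as adjustment variables". The abstract names both together: "Univariate and multivariable linear regression will be used to analyze the primary outcome". The one-month score is to be handled by the same procedure.

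The baseline score is available for this purpose. Under section 2.3, after the demographic form, "participants will be redirected to a first 50-question quiz designed to assess their baseline knowledge", and the training material follows only after that quiz.

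The prior-knowledge term in the second model is not that score. Section 2.2 describes it as a randomisation stratum: "prior NIHSS knowledge (limited, moderate, or extended), and institution by virtue of specific links displayed on the front page". Participants choose it before they answer any quiz question.

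**The concern.** Subtracting the baseline is not the same as adjusting for it. An unadjusted change score fixes the coefficient of post on pre at exactly 1. If the true slope is different, part of the baseline variation stays in the outcome as noise, and a chance baseline difference between arms moves the estimated effect. A model containing the baseline score estimates the slope and removes that noise.

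Precision is at stake. The trial needs 72 participants from 120 invitations, a 60% participation rate, and section 3.2 warns that attrition may be high. A gain that needs no extra participants is worth having. The covariate list is also explicit, so leaving the baseline score out is a stated choice and not a detail deferred to another document.

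**Working it through.** **Inputs from the article.** Section 2.7: "Seventy-two participants are required to have 80% chance of detecting a difference of 2 points", at the 5% level, with the difference defined on the post-course quiz. It gives no SD, pre-post correlation, allocation ratio or sidedness. I assume 1:1 allocation (36 per arm) and a two-sided test.

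**Step 1: the SD behind 72.** Per arm, n = 2·SD²·(1.960 + 0.842)² / 2². Solving for SD at n = 36 gives 3.03 (normal) or 2.99 (t-test). In the other direction, SD = 3.0 gives 2 × 9 × 7.85 / 4 = 35.3, rounded up to 36 per arm and 72 in total. So 72 is consistent with an SD of about 3.0. That figure is inferred, not stated.

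**Step 2: residual variances.** With ρ the pre-post correlation and β = ρ·SDpost/SDpre the slope of post on pre:

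- baseline-adjusted: SDpost²·(1 − ρ²)
- unadjusted change: SDpost²·(1 − ρ²) + (1 − β)²·SDpre²

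The second exceeds the first by (1 − β)²·SDpre², which is zero only if β = 1. With equal SDs, β = ρ, and the variances become 2·SD²·(1 − ρ) for change and SD²·(1 − ρ²) for the adjusted analysis. Their ratio, adjusted to change, is (1 + ρ)/2.

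**Step 3: power at 36 per arm.** Effect 2 points, post-score SD 3.0, equal pre and post SDs, noncentral t with noncentrality 2 / (SD·√(2/36)):

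| ρ | SD, change | SD, adjusted | Power, change | Power, adjusted | Variance saved |
|---|---|---|---|---|---|
| 0.3 | 3.55 | 2.86 | 0.65 | 0.83 | 35% |
| 0.5 | 3.00 | 2.60 | 0.80 | 0.90 | 25% |
| 0.7 | 2.32 | 2.14 | 0.95 | 0.97 | 15% |
| 0.8 | 1.90 | 1.80 | 0.99 | 0.996 | 10% |

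At ρ = 0.5 the standard error is 3.00 × √(2/36) = 0.71 for change and 2.60 × √(2/36) = 0.61 after adjustment.

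**Step 4: if 3.0 is the SD of the change instead.** The change analysis then has about 0.80 power at every ρ. The adjusted SD is 3.0·√((1 + ρ)/2), which gives power of 0.93, 0.90, 0.86 and 0.84 at ρ = 0.3, 0.5, 0.7 and 0.8.

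**Step 5: how much the planned covariates recover.** Take ρ = 0.5. Suppose profession, prior-knowledge category and centre explain a share q of the baseline variance and act on the post score only through the baseline. The adjusted change model then has residual variance 9·[(1 − 0.5)²·(1 − q) + (1 − 0.5²)]. For q = 0.2 to 0.6 the SD is 2.92 to 2.77 and power 0.82 to 0.86. This lies between 0.80 (unadjusted change) and 0.90 (baseline-adjusted).

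**The case against.** The strongest reply is that nothing here is invalid, and that stands. Randomisation makes the change-score contrast unbiased, its test holds 5%, and its standard error already allows for chance baseline imbalance. The stated objective is about improvement, and change is a coherent measure of that. A reader might infer bias from regression to the mean. The documents do not support that: it affects precision and the estimate conditional on an observed imbalance, not the expectation.

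A reader might also infer that the slope must be far below 1, because the quiz is capped at 50 and the sample mixes levels of experience. No score distribution is given, so a ceiling effect is plausible but not shown. People answering the same quiz twice could have a high correlation, and at 0.8 the gain is slight.

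Finally, a reader might infer two competing primary results and an inflated type I error. Section 2.8 is sequential, nothing says that significance in either model suffices, and an analysis plan not shown may name the deciding one. Randomisation is also stratified on the same three factors used as adjusters. In simulations at N = 72, the chance under the null that at least one model is significant was about 6 to 8% with simple allocation that gives no balance, but about 4.5 to 5.7% with blocking within strata. The article does not say whether blocks are used. This is at most a conditional concern.

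The reply does not remove the omission: the covariate list is fixed and lacks the baseline score, and the three-level category stands in for it only in part.

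**Conclusion.** The point holds as one of efficiency. Both planned models are valid, and both are less precise than one containing the baseline score unless the post-on-pre slope is 1 or, for the adjusted change model, the listed covariates already capture the baseline. Against unadjusted change, the variance saving is 35% to 10% for correlations of 0.3 to 0.8 with equal SDs. If 3.0 is the SD of the post score, unadjusted change falls below 80% power when the correlation is under about 0.5; above 0.7 both analyses are well powered. Against the planned adjusted change model the gain is smaller. All power figures rest on the back-solved SD, 1:1 allocation, a two-sided test and the assumed correlations. This is a recommended improvement of uncertain size, not an error that threatens the trial's conclusion.

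**What to change.** In section 2.8, add the continuous baseline quiz score to the multivariable model alongside profession, prior NIHSS knowledge and work center, and name this model as the primary analysis. Report the adjusted difference between arms with its 95% CI. The outcome may be the post-course score or the change: since post = a + b·arm + c·pre is the same as change = a + b·arm + (c − 1)·pre, the arm coefficient b is identical. The change definition in section 2.6 can therefore stay, and the estimate also corresponds to the post-course difference on which section 2.7 is powered.

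Keep the univariate model as supportive, and apply the same baseline adjustment to the one-month score. Naming one model also removes the conditional type I error question.

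The cost is a sentence or two and one degree of freedom, with no new data and no additional participants. The change should be made before outcome data are seen.

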### 2.4. Learning Material

The control group will follow the traditional didactic video created by Dr. P. Lyden [20], USA, which we have subtitled in French [31]. Meanwhile, the e-learning group will be presented with version 21c of our e-learning module [32]. This module was created using Storyline 3 (Articulate Global Inc., New York, NY, USA) and contains 184 interactive slides. Its structure follows the logic supporting the NIHSS (Figure 2).

Participants are required to go through all 12 chapters before reaching the final chapter, which summarizes the entire NIHSS score. Video extracts taken from the original didactic video have been embedded in each chapter (Figure 3), as their presence has been shown to improve knowledge acquisition [19].

In this module, quizzes and feedback [33,34] are used extensively to enhance learner engagement and promote knowledge acquisition (Figure 4). Whenever the learner gives a wrong answer, the feedback message includes the possibility to review the scoring logic related to the specific NIHSS item being tested.

Depending on the complexity of the item, specific animations or interactions are used to facilitate knowledge acquisition. This is for example the case for visual fields (Figure 5) and for extinction/inattention (Figure 6).

After completing the learning material, participants will be asked to answer the same 50-question quiz to determine their knowledge acquisition. At the end of this quiz, a post-course satisfaction questionnaire will be displayed (Table 2).

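### Quiz and course times are compared without the stratification factors or time on the identical pre-training quiz: a valid test, but less precise than the design allows

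*Protocol article*

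**What the plan says.** Section 2.6 lists the time outcomes among the secondary outcomes: "time to course and quiz completion, user satisfaction with the learning method". Section 2.8 describes the handling of "time for course completion and time for quiz completion, will be done graphically", with a Shapiro–Wilk test in case of doubt, and continues: "Then, a Student’s unpaired t-test or the Mann–Whitney U test will be applied". It names no covariate for these comparisons and does not say which sitting of the quiz is meant.

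Three other statements bear on this:

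- **The quiz is taken before training.** Section 2.3: "participants will be redirected to a first 50-question quiz designed to assess their baseline knowledge".
- **The identical quiz is taken after training.** Section 2.4: "participants will be asked to answer the same 50-question quiz to determine their knowledge acquisition".
- **Strata exist and are used elsewhere.** Section 2.2: "Randomization will be stratified according to professional status (nurse or resident physician), prior NIHSS knowledge (limited, moderate, or extended), and institution". For the primary outcome, section 2.8 says that "a multivariable linear regression model will be generated with profession, prior NIHSS knowledge, and work center as adjustment variables", and the one-month quiz analysis "will follow the same procedure as the primary outcome".

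**The concern.** Time on the first quiz is measured before a participant sees any training material, on the same 50 questions as the second quiz. It is the natural baseline covariate for second-quiz time, and an unpaired two-sample test leaves it out. The same section adjusts the score outcomes for profession, prior NIHSS knowledge and work center but not the time outcomes, and gives no reason for the difference.

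What is at stake is the width of the interval and the power of a secondary comparison with 72 participants. The point concerns omitted covariates, not the choice between a t-test and a rank test. Course time has no pre-training counterpart, so for that outcome only the stratification factors are at issue.

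**Working it through.** **Inputs from the article.** 72 participants in total and a 5% significance level (section 2.7); the same quiz before and after training (2.3, 2.4); strata of profession (2 levels), prior knowledge (3 levels) and institution (2.2). Section 2.9 refers to two university hospitals.

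**Assumed, because the article does not give them.** 1:1 allocation (36 per arm), a two-sided test, the correlation ρ between log first- and log second-quiz time, and the spread of quiz time.

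**The plan's own figure.** The article states no figure for quiz time. The 72 belongs to the score outcome and needs an SD that section 2.7 does not state. With an assumed SD of 3.0 points, the two-sided two-sample formula for a 2-point difference gives 36 per arm, or 72 in total. Also, 72/120 = 60%, as stated. The point below does not depend on that SD.

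**1. Gain from first-quiz time.** With a baseline covariate the residual variance is multiplied by 1 − ρ², and the equivalent unadjusted sample size is 72/(1 − ρ²). The detectable difference at 80% power, by the normal approximation with 36 per arm, is (1.96 + 0.84) × √(2/36) × √(1 − ρ²) SD units.

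| Assumed ρ | 1 − ρ² | Variance cut | Equivalent N | Detectable difference (SD) |
|---|---|---|---|---|
| 0 (unadjusted) | 1.00 | 0% | 72 | 0.66 |
| 0.3 | 0.91 | 9% | 72/0.91 ≈ 79 | 0.63 |
| 0.5 | 0.75 | 25% | 72/0.75 = 96 | 0.57 |
| 0.6 | 0.64 | 36% | 72/0.64 = 112.5, so 113 | 0.53 |
| 0.7 | 0.51 | 49% | 72/0.51 ≈ 141 | 0.47 |

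**2. The same gain as power.** Take an assumed log-SD of 0.4 and a true 20% shorter time. The standardized difference is |ln 0.8|/0.4 = 0.223/0.4 = 0.558. By the noncentral t distribution, unadjusted power is 0.65. Dividing 0.558 by √(1 − ρ²) gives power of 0.69, 0.77, 0.83 and 0.90 at ρ = 0.3, 0.5, 0.6 and 0.7. The suggested model has seven coefficients (intercept, arm, one for profession, two for knowledge, one for center, one for log first-quiz time), which leaves 72 − 7 = 65 degrees of freedom instead of 70. That changes these powers by about 0.001 or less.

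**3. Effect of ignoring the strata.** A simulation used 2 × 3 × 2 = 12 strata of six people, split evenly between arms within each stratum, with 4,000 replicates and no true effect. The unadjusted t-test at a nominal 5% rejected in 5.2% of replicates when the strata explained none of the variance. When they explained 10%, 20% and 30%, it rejected in 3.7%, 2.8% and 1.9%. The test is then conservative: its standard error still contains between-stratum variation that the randomization has already balanced. This applies to course time as well as quiz time. It relies on the arms being balanced within strata, which the simulation imposed.

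**The case against.** The strongest reply is that nothing here is an error. An unpaired comparison of randomized arms is valid, the outcome is secondary with no power target, and an article need not list every covariate. The first two points stand and keep this minor. The third carries less weight, because section 2.8 does fix the method for these outcomes, and beside it sets out an adjusted model for the scores.

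A second reply is that the correlation may be weak. The quizzes are taken online without supervision. Section 3.2 concedes that outside resources or group completion cannot be ruled out and that the temptation to look things up is greatest at baseline, so first-quiz time may include look-up time. The second sitting also repeats questions already seen. This stands: no correlation is documented, and at 0.3 the gain is only 9% of the variance. A log-linear model also brings its own distributional assumption, and a rank test is a reasonable choice if the times are irregular.

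Third, the article does not say that first-quiz time is recorded. That stands too and makes this part of the change conditional. Adjustment for the strata needs no further data.

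A reader might infer something stronger: that working speed dominates quiz time, or that chance imbalance in speed or knowledge will be mistaken for an effect of the material. The documents do not support either. They give no variance or correlation for time, stratification limits imbalance in the three factors, and chance imbalance in speed is already covered by the test's error rate.

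**Conclusion.** The point holds as a modest one about efficiency. Section 2.8 fixes unadjusted tests for both time outcomes although the three stratification factors are to hand and the identical quiz precedes training. The comparison remains valid and free of systematic bias, and neither the primary outcome nor the planned 72 participants is affected.

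For quiz time the size depends on an unknown correlation: from almost nothing gained at 0.3 to about half the variance removed at 0.7. For course time only the strata matter, and their contribution depends on how well they predict time. The figures rest on 1:1 allocation and, for the power values, on the assumed log-SD and effect. The conservatism also needs balance within strata.

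**What to change.** In section 2.8:

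1. State that the between-arm comparison of quiz time uses the second, post-training quiz. First-quiz time should not be tested as an outcome.
2. Analyse log second-quiz time by linear regression on arm, profession, prior NIHSS knowledge and work center, adding log first-quiz time if the platform records it. Report a ratio of geometric means with a 95% confidence interval.
3. Analyse log course time on arm and the same three factors.
4. Check residuals as for the primary model, and keep the Mann–Whitney test as a sensitivity analysis if the log model fits poorly.

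The cost is a change of analysis wording, plus confirmation that first-quiz time is logged. The downsides are interpretation on a ratio scale and reliance on a log-linear model. The wording should be settled before the data are unblinded, so that the covariates are prespecified.

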Digital learning resources play an important role in education today [15]. Over the last decade, e-learning modules have become popular in health professional education [16,17]. Medical and paramedical personnel often work in shift patterns, thus greatly limiting their availability for traditional teaching sessions. E-learning modules are very helpful in this setting, as the content can be viewed without time constraints, can be interrupted and resumed as needed, and can be highly interactive. Self-paced highly interactive e-learning modules have been shown to improve user satisfaction [18,19].

Traditionally, the NIHSS has been taught using a didactic video created by Dr. P. Lyden [20], which is freely available on the internet [21]. Although usually effective in teaching medical procedures [22], videos lack interactivity, making them less engaging than interactive learning materials. However, engagement has been shown to improve knowledge acquisition [23,24].

To enhance learner engagement, we have created a highly interactive electronic learning (e-learning) module using Storyline (Articulate Global, Inc., New York, NY, USA). This module was shown to be more effective than the traditional didactic video in paramedics [18] and in medical students [19]. However, the two prior studies assessing the impact of this e-learning module were carried out in populations naïve to the use of this scale. Moreover, these studies were not designed to determine an effect on knowledge retention.

With time, nurses and physicians working in a stroke unit might have forgotten or overlooked certain key aspects of the application of the NIHSS. We hypothesize that our e-learning module might be more effective in reminding them of the principles underlying the application of the NIHSS than the traditional didactic video. We furthermore hypothesize that knowledge retention at one month should be higher after following this module.

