## 3. Discussion

### 3.1. Main Considerations

This prospective, multi-centric, web-based, triple-blind (participants, investigators, data analyst) randomized controlled study comparing video-based and e-learning should help determine if a highly interactive e-learning module improves NIHSS knowledge and skills more efficiently than the traditional didactic video amongst a mixed population of stroke unit, neurology and neurosurgery ward nurses, and physicians with different levels of experience and expertise.

Results of previous studies have shown that knowledge acquisition was higher in medical students than in paramedics [19]. This is probably due to a better understanding of the neurological system and of clinical testing, even though participants within both groups had no prior NIHSS knowledge. The current study is the first to test the impact of the e-learning module on a population with pre-existing NIHSS knowledge.

Further, we should also be able to determine the impact of these learning modalities on knowledge retention at one month. The decline in performance has been shown to be nonlinear; among participants displaying a significant decline in knowledge retention at 3 months, half of them present a significant decline already after 4 weeks [35]. This time interval has been recently used [36]. Electronic health (e-health) literacy was already high in some countries prior to the COVID-19 pandemic [37] and should have considerably increased in the wake of this crisis. Therefore, determining the most efficient asynchronous distance learning modality to help health care workers improve their NIHSS knowledge is both timely and relevant.

Given the importance the NIHSS score plays in the diagnosis, treatment decisions, and follow-up of stroke patients [1], it is essential to ensure that the NIHSS application skills are maintained at a high level. The study design should also help us gain knowledge of the current performance of neurology and neurosurgery nurses and physicians, prior to any teaching intervention, by virtue of the first (baseline) quiz. This could help determine the necessity of recurrent training in these highly specialized wards to maintain high performance in NIHSS application. There is little reason to believe that the potential decline in NIHSS application knowledge this study could reveal would be different in other settings or countries, and the results obtained should therefore be generalizable.

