**Figure 6 healthcare-09-01460-f006:**
[figure not shown]
Interactive slide used to remind or teach the concept of extinction.

**Table 1 healthcare-09-01460-t001:** First questionnaire.

Page	Field	Original Question	English Translation
1	Demographics	Age	Age ^a^
		Genre	Gender ^b^
		Années d’expérience clinique au total	Number of years of total clinical experience ^a^
		Années d’expérience clinique dans un service de neurologie et/ou de neurochirurgie	Number of years of clinical experience in a neurology and/or neurosurgery ward ^a^
		Maîtrise du Français	French proficiency ^c^
		Maîtrise de l’Anglais	English proficiency ^c^
		Dans quel service travaillez-vous principalement: Unité Cérébrovasculaire—surveillance continue Unité Cérébrovasculaire-étage Etage de neurologie Soins intermédiaires de neurologie Etage de neurochirurgie Soins intermédiaires de neurochirurgie Autre	In which ward do you most frequently work: ^b^ Stroke unit-surveillance unit Stroke unit-regular ward Neurology ward Neurology intermediate care unit Neurosurgical ward Neurosurgical intermediate care unit Other
2	Prior NIHSS knowledge	Avez-vous effectué une formation interne du service pour apprendre à faire une évaluation NIHSS?	Have you completed an in house NIHSS training? ^b^
		Avez-vous complété une formation certifiante officielle NIHSS?	Have you completed the official NIHSS certification course? ^b^
		Nombre d’années de pratique avec l’échelle NIHSS	Number of years of clinical experience with the NIHSS scale ^a^
		Fréquence d’application du NIHSS: Plusieurs fois par jour Environ 1 fois par jour Environ 1 fois par semaine Environ 1 fois par mois Très rarement ou jamais	NIHSS use frequency: ^b^ Many times per day Circa once a day Circa once a week Circa once per month Almost never or never
		Je me sens à l’aise par rapport à l’application du NIHSS	I feel comfortable using the NIHSS ^c^

^a^ Regex: regular expression validation. ^b^ MCQ: multiple-choice question (only one answer accepted). ^c^ 5-point Likert scale.

**Table 2 healthcare-09-01460-t002:** Post-course questionnaire.

Page	Field	Original Question	English Translation
1	Prior NIHSS learning method exposition	Aviez-vous déjà suivi cette méthode de formation au NIHSS?	Had you already been exposed to this NIHSS learning method in the past? ^a^

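### The exclusion planned for the sensitivity analysis cannot be carried out, because the questionnaires record prior use of the allocated material only

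*Protocol article*

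**What the plan says.** Section 2.8 defines the exclusion by either material: "A sensitivity analysis will be performed by excluding those who have previously followed either the e-learning module or the video". It does not vary by arm.

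The item on earlier use of a material is in Table 2: "Had you already been exposed to this NIHSS learning method in the past", in the French original "Aviez-vous déjà suivi cette méthode de formation au NIHSS". Both wordings are singular. Section 2.4 fixes the timing, after the allocated material and the second quiz: "At the end of this quiz, a post-course satisfaction questionnaire will be displayed (Table 2".

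Table 1, completed before the baseline quiz, has two items on earlier training: "Have you completed an in house NIHSS training" and "Have you completed the official NIHSS certification course". Its other items under prior NIHSS knowledge cover years of practice, frequency of use and comfort with the scale. None mentions the video or the module.

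Two background statements bear on how common earlier exposure may be. Section 1.1 says: "Traditionally, the NIHSS has been taught using a didactic video". Section 3.1 says: "The current study is the first to test the impact of the e-learning module on a population with pre-existing NIHSS knowledge".

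**The concern.** The rule needs two facts per participant (ever used the video, ever used the module), and the forms collect one. Which one they collect depends on the arm. A person who learned from the video years ago is identified and removed if allocated to the video, but is not identified and stays if allocated to e-learning. The reverse holds for someone who has used the module.

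Exclusion thus becomes a function of allocation. A subset defined the same way in both arms from pre-study history would keep the balance that randomization provides, apart from chance; this subset does not. The purpose of the analysis is to show whether the result holds among staff new to both materials, and that question would go unanswered. A difference from the primary result could come from the unequal exclusion alone, and so could an agreement with it.

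**Working it through.** **Step 1. Rule against data.** There is no stated figure to reproduce, so the first check compares what the rule needs with what the forms record.

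| Earlier exposure | Rule in section 2.8 | Video arm, with the Table 2 item | E-learning arm, with the Table 2 item |
|---|---|---|---|
| Video only | exclude | excluded | kept |
| Module only | exclude | kept | excluded |
| Both | exclude | excluded | excluded |
| Neither | keep | kept | kept |

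The first two rows fail, each in one arm. The Table 1 items cannot repair them: in-house training and certification do not say which material was used.

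**Step 2. Inputs for the size.** The documents give no exposure rates and no effect of exposure on the gain. All of the following are assumptions:

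- pv, the share with earlier video use: 20-60%
- pe, the share with earlier module use: 5-40%
- b, the reduction in quiz gain per earlier exposure: 1-3 points, the same for both materials
- pv and pe equal across arms by randomization, and the two exposures independent of each other
- no true difference between the arms
- 36 per arm, an equal split of the 72 in section 2.7

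**Step 3. Formula.** Let G be the mean gain of someone exposed to neither material. After exclusion on the Table 2 item:

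- the video arm still contains a share pe of earlier module users, so its mean gain is G - b × pe
- the e-learning arm still contains a share pv of earlier video users, so its mean gain is G - b × pv
- shift (e-learning minus video) = -b × (pv - pe)

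Under the rule as written, both arms lose the share 1 - (1 - pv)(1 - pe), and the shift is 0.

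**Step 4. Results.**

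- Example with pv = 40%, pe = 10%, b = 2: shift = -2 × (0.40 - 0.10) = -0.6 points. Remaining: video 36 × 0.60 = 21.6, e-learning 36 × 0.90 = 32.4. With both exposures recorded: 36 × 0.60 × 0.90 = 19.4 in each arm, with shift 0.
- Most negative value in the range, with pv = 60%, pe = 5%, b = 3: -3 × 0.55 = -1.65 points.
- Most positive value, with pv = 20%, pe = 40%, b = 3: -3 × (-0.20) = +0.6 points.
- Equal exposure (pv = pe), or b = 0: shift 0.

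The target difference in section 2.7 is 2 points.

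**The case against.** **Only a supporting analysis is affected.** The univariate and multivariable regressions of the primary outcome, and the retention analysis, do not use this item. This stands and limits the severity. It is also the only sensitivity analysis that the article names, but a separate analysis plan could hold others.

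**The article may condense the forms.** This carries little weight. Both questionnaires are printed item by item in two languages with their response formats, and the point is that two stated elements do not fit together.

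**Adjustment may absorb some of the imbalance.** Self-declared prior NIHSS knowledge is a stratification factor and an adjustment variable. If the same multivariable model is run in the subset, part of the shift could be removed, and the calculation above is unadjusted. This stands in part: knowledge level is not the same as having used a given material, and the article does not say which model the sensitivity analysis uses.

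**Stronger readings that the documents do not support.**

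- A reader might infer that the exclusion works against e-learning and would tend to contradict the primary result, since the video is the traditional method. Unequal exposure is plausible for that reason. But no exposure rate is given, nothing says that exposed staff gain less, and earlier module use pulls the other way. The sign is open.
- A reader might add that the item is missing for those who stop early. Anyone who stops before the end of the second quiz has no primary outcome and could not enter the analysis anyway. Only someone who finishes the quiz and skips the questionnaire is lost.
- A reader might add that e-learning participants who recognise the embedded video extracts will answer yes by mistake. That is speculation, and it would remove some earlier video users from the e-learning arm too, which reduces the asymmetry.

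**Conclusion.** The mismatch is certain and rests on no assumed figure: the exclusion in section 2.8 needs information that Tables 1 and 2 do not collect, and the item that exists would remove different people from each arm. What follows numerically is conditional. Under the simple model the shift depends on the gap between the two exposure rates and on how far exposure lowers the gain, and it vanishes if exposures balance or have no effect. The upper end of the assumed range is a large fraction of the target difference (1.65 / 2 = 83%), while the worked example is modest (0.6 / 2 = 30%). This should be settled before launch so that the sensitivity analysis can be interpreted. It is no reason to doubt the primary comparison.

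**What to change.** Replace the single Table 2 item with two yes/no items, put to every participant in both arms:

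1. *Before this study, had you ever followed the didactic NIHSS video?*
2. *Before this study, had you ever followed the interactive NIHSS e-learning module?*

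Give a short description of each material, since a participant will have been shown only one of the two in full. The existing follow-up question on timing can be attached to each item.

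Keep both items in the post-course questionnaire. Placing them in Table 1 would name both arms before training in a trial that section 2.1 describes as blinding its participants. It would not make the answers pre-randomization either, because section 2.2 randomizes on the front-page link, before the first questionnaire.

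In section 2.8, state that anyone answering yes to either item is excluded, identically in both arms, and name the model used in the remaining subset.

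The cost is two short items in place of one and one or two sentences in section 2.8. The answers will be self-reported after training, so some recall error remains.
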